# The FitSpirit approach for increasing physical activity in canadian teenage girls: protocol of a longitudinal, quasi-experimental study

**DOI:** 10.1186/s12889-021-10200-5

**Published:** 2021-01-28

**Keywords:** Adolescent girls, Extra-curricular intervention, Health, Lifestyle, Physical activity, Quantitative methods, School-based program

## Abstract

**Background:**

Worldwide, most adolescent girls do not meet physical activity (PA) recommendations and very few PA programs are tailored specifically towards them. Even fewer information exists about the long-term effects of such programs. Some Canadian schools have implemented the FitSpirit PA intervention designed specifically for girls aged 12 to 17 years old. This paper describes the protocol of a quasi-experimental study evaluating long-term changes in health behaviours and outcomes following FitSpirit participation.

**Methods:**

The study is conducted among schools that partner with FitSpirit every year. It started in 2018 and will be completed in 2022. The intervention comprises motivational talks, a turnkey running program, PA sessions and special events. Study participants fill out an online questionnaire twice a year. Follow-up questionnaires are sent at the end of each school year to the study participants who dropout from FitSpirit. The main outcome, changes in PA levels, is evaluated using questions validated for adolescents. Secondary outcomes are health (perceived health); lifestyle habits (sedentary activities, eating and sleeping habits); psychosocial outcomes (physical self-efficacy and body satisfaction); and FitSpirit appreciation (activity participation and satisfaction). Most questions originate from questionnaires validated for the adolescent population. Cross-sectional and longitudinal analyses will be performed.

**Discussion:**

This study will provide one of the first longitudinal reports on the impact of a large extra-curricular PA intervention designed specifically for adolescent girls. The current study will uniquely contribute to PA research by assessing outcomes additional to PA levels, including markers of health, lifestyle habits and psychosocial determinants.

**Trial registration:**

NCT, NCT03804151, Registered on January 22, 2019; retrospectively registered.

**Supplementary Information:**

The online version contains supplementary material available at 10.1186/s12889-021-10200-5.

Nevertheless, a limited but growing number of school-based girl-only PA interventions have been reported [13–18]. In addition, studies that evaluated school-based interventions for adolescent girls on PA levels generally have a small sample size [13], with only two known studies that used a sample larger than 1000 adolescent girls [18–20]. In the literature, there are also very few girl-only extra-curricular interventions [13]. Most meta-analysis and studies on PA for girls solely evaluated the intervention’s effect on PA levels [11–13, 21, 22], neglecting to assess global outcomes of interest, such as health, lifestyle including sedentariness and psychosocial markers. There is some preliminary evidence that PA programs could improve sleep quality of adolescents, but no analyses have been performed by sex [23]. However, there is some evidence that girls-only PA interventions could yield improvements in eating habits [24] and different fitness markers [25, 26]. Furthermore, our recent systematic literature search showed that evidence on the physiological and psychological effects of PA programs designed for adolescent girls is limited and comes from studies of moderate methodological quality [27]. Interestingly, very few of these studies evaluated self-efficacy, though there is a growing interest on the topic [18]. In addition, long-term assessments of participants has been highlighted as a current limit in this field of research [27].

Evidence to date highlights the need for additional longitudinal studies, with a large sample size, conducted in real-life settings to draw clearer conclusions on the effects of school-based PA interventions specifically tailored to adolescent girls. Real life studies inform on the effectiveness of interventions implemented in routine circumstances [28]. FitSpirit is a non-for-profit organization that has been offering school-based, girl-only PA program in Canada since 2007. Their intervention is promising due to the non-competitive and mobilization approaches but remained understudied. In 2017–2018, over 12,000 girls participated regularly in FitSpirit activities delivered in 250 partner schools. Through their activities and event offerings, FitSpirit aims to get adolescent girls moving, and keep them physically active over the long term. The objective of this article is to describe the protocol used to evaluate the changes resulting from the implementation of the FitSpirit approach in schools. It presents a longitudinal, quasi-experimental, non-controlled study that aims to evaluate the following outcomes:

Primary outcome: Changes in PA levels among teenage girls who take part in FitSpirit activities in their school.

Secondary outcomes: Health (perceived health); lifestyle habits (sedentary activities, eating and sleeping habits); and psychosocial determinants (physical self-efficacy and body satisfaction) associated with the FitSpirit program. The study also aims to evaluate the girls’ level of participation as well as their appreciation towards some aspects of the FitSpirit approach.

## Methods

The present article has been written following the guidance of the Standard Protocol Items: Recommendations for Interventional Trials (SPIRIT) [29], as suggested [30]. See Additional file 1 for more details.

### Design of the FitSpirit approach

FitSpirit partners with schools to provide activities that get young girls moving and keep them physically active over the long term. It offers tools and services within a holistic approach based on flexible, individualized support to help schools engage girls through girl-only activities tailored to their challenges and their preferences. Non-competitive group activities are planned, organized and led by a member of the school staff, the school program leader, with the support from a regional coordinator. The physical and health education teacher, or any other school employee, can become the FitSpirit school leader. FitSpirit activities can run during the entire school year, with most schools organizing activities only between February and May and for a minimum of 8 weeks (unpublished data). For example, only 67 of the 285 partner schools registered in the school year 2018–2019 have organized FitSpirit activities during fall. In addition, during this same school year, an average of 19 activities have been organized by the partner schools.

FitSpirit offers its support through several services, but mainly the ones listed below. Each partner school decides the extent to which they use and exploit these every year and this information is collected by FitSprit in order to conduct a process evaluation.
FitSpirit Ambassadors: Ambassadors are dynamic, passionate women who inspire girls and motivate them to be physically active. They act as accessible role models while representing the organization in diverse settings. Their message is conveyed through motivational conferences delivered in school. They also lead various PA sessions as a way to introduce girls to different ways of being active, such as yoga classes, zumba, bootcamp, rugby, orienteering, etc. The school leaders choose which activity is best for participants. Every year, more than 150 women take on this role for FitSpirit.An interactive web platform that includes a dynamic tool for choosing workouts, tips for being active, videos, recipes, and the service of a nutritionist and a kinesiologist to answer questions.An 8–10-week turnkey running program: The program suggests an 8-week exercise progression including strength and intervals trainings. It has been developed for adolescents’ girls. Exercise intensity is determined using a perceived exertion scale.Major events: Yearly, FitSpirit holds a series of events that bring together thousands of girls for a memorable, high-energy day of PA and togetherness. Participants can tackle a range of exciting challenges, from completing a not-timed 5 K or 10 K run, to trying out any number of fun new activities (e.g. baseball, obstacle course, judo, ultimate Frisbee). Every girl, regardless of skill or fitness level, is invited to pursue her discovery of sports, PA and the great outdoors.FitSpirit training: Yearly, in-person training sessions aimed at program leaders and ambassadors are delivered in several locations. Webinars and online tools are also available to those who are unable to attend. The training provides: 1) Hands-on tools for the FitSpirit community to help them communicate the joy and benefits of adopting a healthy lifestyle; 2) Leadership and outreach training for Student Leaders; 3) Continuing education courses and tools specially tailored to the priorities and challenges identified by FitSpirit; 4) Spaces for the FitSpirit community to share knowledge and best practices.

Readers are invited to visit the website (www.fitspirit.ca) for further information about the FitSpirit approach.

### Study population

All Canadian schools with girls 12–17 year old are invited to implement the FitSpirit approach. Yearly, between 250 and 300 schools from the provinces of Quebec and Ontario become FitSpirit partners. School boards, principals and teachers learn about the organization through advertisement, word-of-mouth and their regional coordinator. A regional coordinator acts as an advisor, a resource person and an advocate for PA in the community and is the FitSpirit liaison for the field team in each geographic area. This person contributes to the promotion and deployment of the approach in non-partner schools. It is up to each school to decide whether all or only a limited group of the female student population will participate in the activities and events planned by the school. Although the approach aims to encourage inactive girls to participate, this is not a participation criterion and therefore all are welcomed. Therefore, FitSpirit participants have mixed sport backgrounds and abilities.

The FitSprit registration process includes an invite to provide consent for the participation of the girls in the research project. As required by the Quebec law, participants younger than 14 have to provide one parent’s written informed consent and those aged 14 years and older can provide their own written consent. Information and consent form is available online (fillactive.com). The FitSpirit organization collects research consent information because they transfer only anonymous data to the research team. Figure 1 shows the timeline of the data collections within each school year.
Between 2017 and 2019, a stratified random sampling method was applied to recruit girls for research. Each school leader randomly selected five to ten research participants among all girls who provided consent, irrespective of grade. The FitSpirit organization sent the invitation to research participants via email and their school leader could help them have access to the online questionnaires at school.By the year 2019–2020, the FitSpirit organization moved towards the invitation of all girls with consent to participate in the research project (15,000 potential participants). FitSpirit send invitations for the research via email and the school leaders are no longer involved in research.For the follow-ups, the same girls are contacted again by the FitSpirit organization, whether or not they still participate in FitSpirit in subsequent years, as illustrated in Fig. 2.Research participants will be contacted for follow-ups each year until May 2022.

**Fig. 1 Fig1:**
[figure not shown]
Schedule of enrolment, intervention, and assessments within a school year

**Fig. 2 Fig2:**
[figure not shown]
Schedule of enrolment, intervention, and assessments over the course of the project

### Data collection

Data are collected by the FitSpirit organization using an online questionnaire (Survey Monkey) available in both French and English. Table 1 presents the variables collected as well as the source of the questions. Most questions come from the Canadian Health Measure Surveys [31, 35] and the *Enquête Québécoise sur la santé des jeunes du secondaire* [32], two large surveys that have been validated for a Canadian teenage population. Moreover, a validation phase for the questionnaire was run among a small group of FitSpirit participants in 2017 where additional in-house questions were tested. Based on the results and the experience gained during this phase, a group of seven co-investigators with complementary expertise in exercise, nutrition, social and health sciences developed the content of the current questionnaire. Many rounds of consultations led to the final content and question order. Table 2 presents the questions used to evaluate PA levels of participant, that is the primary outcome of the study. The Additional file 2 shows the questionnaire to be answered on Survey Monkey by participants at the end of a school year.

**Table 1 Tab1:** Variables measured in the questionnaire and question’s source

Category	Variable
General information	• Age (in-house questionnaire) • School (in-house questionnaire) • School grade (in-house questionnaire) • Postal code (in-house questionnaire)
PA levels (primary outcome)	• Presence of PA facilities in community (in-house questionnaire) • Days per week with 60 min of PA [31] • Time per week using active transportation modes [31] • Time per week in leisure time PA [31] • Group vs. individual PA (in-house questionnaire) • School vs. outside school PA (in-house questionnaire)
Health (secondary outcomes)	• Perceived health status [31] • Weight [32] • Height [32] • Physical or mental health conditions diagnosed [31]
Lifestyle habits (secondary outcomes)	• Food consumption habits [32] • Breakfast eating [32] • Sleep time and somnolence [31] • Screen time per week [31]
Psychosocial outcomes (secondary outcomes)	• Perceived and desired body image [32] • Weight control techniques [32] • Physical self-efficacy [33] • Quality of life [31] • Physical self-esteem [34] • Interest in school [32] • Sense of belonging [35]
FitSpirit appreciation (secondary outcomes)	• Reasons for participation (in-house questionnaire) • Words associated with FitSpirit (in-house questionnaire) • Participation level (in-house questionnaire) • Satisfaction level (in-house questionnaire) • Injuries (in-house questionnaire)

*PA* Physical activity

**Table 2 Tab2:** Questions evaluating physical activity levels

Questions	
• Over a typical or usual week, on how many days are you physically active for a total of at least 60 min in total per day? Consider only the activities that made you breathe harder and sweat at least a little. ○ None (zero days) ○ 1 day ○ 2 or 3 days ○ 4 to 6 days ○ Everyday	
• In the last 7 days, how long did you use active forms of transportation to get around, like walking to school or cycling to get to work, the shopping center or a friend’s place? (Enter hours AND minutes. You can enter 0 h and 0 min if you have not used active modes of transportation.)	
• In the last 7 days, how long did you do physical activity in your leisure time including exercising, playing an organized or non-organized sport or playing with your friends? (Enter hours AND minutes. You can enter 0 h and 0 min if you have not been active during your leisure time.)	

Data are collected at the beginning and at the end of each school year. Study participants are invited via their personal email address provided at registration to complete the online questionnaire. The end of year questionnaire is also sent to study participants who dropped out from FitSpirit. The longitudinal design of the study will allow the research group to perform an assessment over a prolonged period of time. It will also allow for an evaluation of the persistence of the effects of the program over the summer school break.

To ensure participant retention at each data collection period, research participants can enter a draw to win prices. Prices for a total value per year of approximately $1000 are given among participants who fill out the online questionnaire. There is a new draw at each data collection period and participants have one chance to win per period. Data integrity is enforced using different mechanisms. First, participants complete themselves the online questionnaire and answers will be transferred directly into the database. This procedure eliminates the risk of transcription errors. Then, verification for valid values and consistency against data already stored in the database will be performed. The answers to the questionnaires will remain stored online and a password system will be utilized to control access. Databases will also be secured with password-protected access systems.

### Sample size determination

This protocol presents the first attempt to evaluate the overall effect of the FitSpirit approach. The primary outcome of this project is PA level. For our specific population, there is no direct comparative reference that can be used to perform a relevant power calculation. Most studies used accelerometer data to evaluate the impact of their intervention on PA levels and authors used different questions [13]. Since the FitSpirit intervention is applied in many schools covering a large territory, a great number of participants is required to be representative of the various environments where the intervention is used. The authors have thus decided with the organisation to include all participants, leading to a potential sample of 15,000 individuals. For logistical reasons, it is unrealistic to measure objectively the PA levels of all participants. To our knowledge, the largest study to evaluate self-reported PA levels among adolescent girls in response to a school-based intervention included approximately 3000 participants [36]. They observed a significant 8% increase in the proportion of girls who reported engaging in vigorous PA, that is activities assigned at least 6 metabolic equivalents (METs). It is then reasonable to think that 15,000 participants will lead to enough power to detect meaningful changes in PA levels.

### Statistical analyses

The primary research question to be answered relates to the impact of FitSpirit on the participants’ PA level. The secondary research questions relate to the impact of FitSpirit on other lifestyle habits (sedentary activities, eating and sleeping habits), health perception, physical self-efficacy, body satisfaction, and participants’ appreciation of the FitSpirit approach. Both continuous (ex: total minutes of PA/week) and categorical data (ex: meeting or not the recommendation for moderate-to-vigorous PA) will be used as dependent variables, while the number of FitSpirit activities/year and of years of participation at FitSpirit will be used as independent variables. Data will be analysed in a cross-sectional fashion using chi-square test and Fisher’s exact test (depending on the sample size) to evaluate for instance the relationship between categories of PA levels and categories by the number of years of participation in FitSpirit. Pearson’s test will assess, for example, the correlation between the number of days/week meeting PA recommendations and levels of physical self-efficacy. In addition, analyses of variances will compare the levels of PA (total minutes of PA/week) between grade levels. Longitudinal analyses will evaluate primarily the change in PA levels, and in other secondary outcomes afterwards. Statistical adjustments will be performed using, for instance, the variation in the length of intervention from one school to another or the baseline lifestyle habits of participants as covariates.

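### The cross-sectional tests named for FitSpirit exposure treat girls as independent although they are nested in 250–300 schools that set how much of the programme is used

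*Protocol article*

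**What the plan says.** All references are to the Protocol article.

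- **Tests.** Statistical analyses: "Data will be analysed in a cross-sectional fashion using chi-square test and Fisher’s exact test (depending on the sample size"). The example given is PA category against category of years in FitSpirit. A Pearson correlation (active days per week with physical self-efficacy) and an analysis of variance follow: "analyses of variances will compare the levels of PA (total minutes of PA/week) between grade levels".
- **Exposures.** Same section: "the number of FitSpirit activities/year and of years of participation at FitSpirit will be used as independent variables".
- **Nesting.** Study population: "Yearly, between 250 and 300 schools from the provinces of Quebec and Ontario become FitSpirit partners". For 2017–2019: "Each school leader randomly selected five to ten research participants among all girls who provided consent, irrespective of grade". From 2019–2020 all consenting girls are invited, and Sample size determination describes this as "leading to a potential sample of 15,000 individuals".
- **Who sets the dose.** Design of the FitSpirit approach: "Each partner school decides the extent to which they use and exploit these every year".
- **Adjustment offered.** Statistical analyses gives length of intervention by school and baseline habits as examples of covariates. The article mentions no clustering, ICC, mixed model, GEE or robust variance.
- **Longitudinal part.** Change in PA is to be analysed longitudinally, with no method named.

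**The concern.** In standard form, chi-square and Fisher's exact tests count every girl as an independent unit. Girls in one school share staff, facilities, peers and neighbourhood, so their PA is likely to be correlated. They also share, at least in part, the exposure under test, because the school decides what is offered. When outcome and exposure both cluster by school, the variance of an exposure contrast exceeds what these tests assume, and they reject too often.

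The covariate for length of intervention does not repair this. It adjusts the mean for one feature of the school and leaves the remaining within-school correlation unmodelled. Chi-square and Fisher's tests in standard form take no covariates in any case.

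This is not a detail left for later. The article commits to particular tests for a stated exposure, and those tests do not fit the nested design it describes. Inviting all consenting girls instead of five to ten per school makes the clusters larger, which increases the distortion. At stake is whether a reported cross-sectional link between FitSpirit exposure and PA can be taken at its nominal significance level.

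**Working it through.** **No figure to reproduce.** The article states no alpha, power, standard deviation or ICC, and says that no relevant power calculation was possible. Two-sided alpha 0.05 and ICCs of 0.01–0.05 are therefore assumptions.

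**Inputs from the article.** There are 250–300 schools a year and 15,000 potential participants. That gives 15,000/300 = 50 to 15,000/250 = 60 girls per school if all respond. The 2017–2019 sampling gives 5–10 per school.

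**Formulas.** With m girls per school and an exposure identical for all girls in a school, the design effect is DE = 1 + (m − 1) × ICC. If the exposure is only partly shared, with intraclass correlation rho, DE = 1 + (m − 1) × rho × ICC. The true type I error of a nominal two-sided 5% test is 2 × [1 − Φ(1.96/√DE)]. A correct interval is √DE times as wide as the naive one.

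**Exposure fully shared within school, 15,000 girls**

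| Girls per school | ICC | DE | Effective N | True alpha |
|---|---|---|---|---|
| 50 | 0.01 | 1.49 | 10,067 | 10.8% |
| 50 | 0.02 | 1.98 | 7,576 | 16.4% |
| 50 | 0.05 | 3.45 | 4,348 | 29.1% |
| 60 | 0.01 | 1.59 | 9,434 | 12.0% |
| 60 | 0.02 | 2.18 | 6,881 | 18.4% |
| 60 | 0.05 | 3.95 | 3,797 | 32.4% |

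Correct intervals are √1.49 = 1.22 to √3.95 = 1.99 times the naive width.

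**Exposure partly shared.** Take rho = 0.3 (assumed) and m = 15,000/275 = 54.5. DE = 1 + 53.5 × 0.3 × ICC = 1.16, 1.32 and 1.80 at ICC 0.01, 0.02 and 0.05. True alpha is 6.9%, 8.8% and 14.4%.

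**Small clusters, exposure fully shared.** At m = 5 and ICC 0.01, DE = 1.04 and alpha is 5.5%. At m = 10 and ICC 0.05, DE = 1.45 and alpha is 10.4%. If 20% of 15,000 respond across 275 schools (10.9 per school), alpha is 6.2% to 10.9% over the same ICCs.

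**Simulation check.** An ordinary chi-square test was run under the null on beta-binomial data (275 schools × 55 girls, assumed base proportion 0.24).

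| Exposure | Runs | ICC 0.01 | ICC 0.02 | ICC 0.05 |
|---|---|---|---|---|
| Set by school | 1,000 | 11.3% | 15.6% | 35.4% |
| Partly shared (rho about 0.3) | 1,000 | 7.8% | 7.9% | 14.7% |
| Balanced within school | 1,000 | 4.2% | 4.4% | 4.8% |
| Set by school | 6,000 | 12.2% | 16.9% | 30.2% |
| Partly shared (rho about 0.3) | 6,000 | 6.8% | 8.4% | 14.8% |
| Balanced within school | 6,000 | 5.2% | 4.4% | 4.6% |

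The 35.4% lies above the formula value for m = 55 (DE = 1 + 54 × 0.05 = 3.70, alpha 30.8%). The 6,000-run repeat gives 30.2%, so the excess is simulation noise, and the formula values are the ones to rely on.

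**The case against.** The strongest reply is that the primary result is change in PA, to be analysed longitudinally by a method the article does not name. The four tests sit in the cross-sectional part and are partly illustrative. This stands. A reader might infer that the primary longitudinal analysis is invalid, but the article neither includes nor excludes a model with school as a level, and a condensed article may leave that choice to a fuller document.

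A reader might also infer that the tests ignore repeated answers from the same girl. The documents do not support that. The tests are described as cross-sectional, they can be run one wave at a time, and nowhere is pooling of waves stated.

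Nor does the point extend to every named test. The Pearson and analysis-of-variance examples concern self-efficacy and grade, not FitSpirit exposure. For a factor balanced within schools, the simulation shows essentially nominal error.

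Exposure may also be less school-bound than the worst case assumes. Years of participation is a girl's own history and can differ among schoolmates, who were sampled irrespective of grade. Participation level is collected by individual questionnaire (Table 1). Length of intervention is a covariate, not a stated exposure. This limits the size of the problem, not its direction: schools still decide how much of the programme is used, and a partly shared exposure still gives error above 5%.

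**Conclusion.** The point holds for the cross-sectional tests of FitSpirit exposure: chi-square or Fisher's test of PA category by years of participation, and any like test of activities per year. They make no allowance for school. If exposure and PA both cluster by school, their p-values are too small and their intervals too narrow.

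The direction is firm under that condition, but the amount is unknown, because the article gives neither the ICC nor the sharing of exposure. The upper range of about 11–32% needs full response from 15,000 girls and an exposure identical within each school. Partial sharing (rho 0.3) brings it to about 7–15% across formula and simulation, and 5–10 girls per school to about 5.5–10%.

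A reader might infer that the study lacks power once clustering is counted. The figures do not support that. With an assumed split of 7,500 against 7,500 and an 8-point difference from assumed base rates of 14% to 46%, power stays at 96% or more even at ICC 0.10 and 60 girls per school (DE = 1 + 59 × 0.10 = 6.9). The issue is the validity of p-values and intervals.

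**What to change.** - For exposure–PA analyses, replace the simple tests with mixed models (linear for minutes, logistic or ordinal for categories) with a random intercept for school, or use GEE or cluster-robust errors with school as the cluster. Add girl as a level only where waves are pooled.
- For cross-tabulations, use a Rao–Scott corrected chi-square with school as the cluster.
- State that the longitudinal model for change in PA will carry the same school level.
- Report the estimated ICC with the results.

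The cost is a few sentences in the analysis section and standard software. School is already in the questionnaire (Table 1), and 250–300 schools are ample for cluster-based variance estimates. The downside is wider intervals for exposures shared within schools, by up to about twofold at the top of the assumed range and by little where exposure varies mainly within schools.

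### The only test named for PA category by years of participation, chi-square or Fisher's exact, ignores the order of both variables

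*Protocol article*

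**What the plan says.** The protocol article's Statistical analyses section sets out the outcomes and exposures together. On the outcome side, both continuous and "categorical data (ex: meeting or not the recommendation for moderate-to-vigorous PA) will be used as dependent variables". On the exposure side, "the number of FitSpirit activities/year and of years of participation at FitSpirit will be used as independent variables".

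For the cross-sectional part it states: "Data will be analysed in a cross-sectional fashion using chi-square test and Fisher’s exact test (depending on the sample size"). It gives the purpose as "to evaluate for instance the relationship between categories of PA levels and categories by the number of years of participation in FitSpirit". No other test is named for years of participation.

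The section also plans longitudinal analyses of change in PA as the main focus, and covariate adjustment, but names no model for either.

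The weekly-days item in Table 2 offers five ordered answers: "None (zero days) ○ 1 day ○ 2 or 3 days ○ 4 to 6 days ○ Everyday". The article does not say whether these five answers are the PA categories meant in the cross-table, and it fixes no cut points for years.

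**The concern.** Whether PA is higher among girls with more years in the program is a directional question about two ordered variables. Pearson chi-square and Fisher's exact test do not use that order. Shuffling the rows or columns leaves the result unchanged, and any irregular pattern can produce a small p-value. A significant result therefore does not show that PA rises with years, nor by how much.

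The evidence is also spread over (rows − 1) × (columns − 1) degrees of freedom, where a trend test uses one. If the relation is graded and modest, this comparison is more likely to miss it.

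This matters more than it would in a controlled trial. The study has no control group, so graded exposure is one of its few internal contrasts. The plan is also uneven: its next example correlates days per week with self-efficacy by Pearson's test, which does use the order of the days variable.

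**Working it through.** **The plan's own figure.** There is none to reproduce. The Sample size determination section says "there is no direct comparative reference that can be used to perform a relevant power calculation" and decides to "include all participants, leading to a potential sample of 15,000 individuals". The 15,000 is a count of girls who can be invited, with no alpha, power or effect size behind it.

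**Does the test see order?** Take a 3×3 table with a clear gradient, rows (10, 20, 70), (20, 30, 50), (40, 30, 30). Pearson chi-square is 38.5 in natural order, with the rows reversed, and with the first two rows swapped. It carries no order and no direction.

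**Cost in degrees of freedom.** At two-sided alpha 0.05 (assumed; the article states none), the non-centrality needed for 80% power is:

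| Test | df | Non-centrality | Ratio to trend test |
|---|---|---|---|
| Trend | 1 | 7.85 | 1 |
| Binary PA × 4 year categories | (2−1)(4−1) = 3 | 10.90 | 1.39 |
| 5 PA levels × 4 year categories | (5−1)(4−1) = 12 | 17.34 | 2.21 |
| 5 PA levels × 5 year categories | (5−1)(5−1) = 16 | 19.27 | 2.45 |

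For a purely linear trend, the ratio is the factor by which the sample must grow. Four or five year categories is an assumption, taken from the study window ("It started in 2018 and will be completed in 2022").

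**Power in concrete settings.** Inputs:
- 14% in the top PA level at one year. This is the Background's figure for girls, read as the share meeting the recommendation.
- Other PA levels 8/15/38/25% (assumed).
- Years split 55/25/13/7% (assumed).
- A constant proportional-odds shift per year category, with girls treated as independent (assumed).
- N=3,000 is 10 girls × 300 schools and N=1,250 is 5 × 250 schools, the limits of the 2017–2019 sampling. N=15,000 is the full pool.

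Odds ratio per year category = [odds at the fourth category ÷ odds at the first]^(1/3):
- To 16%: (0.1905/0.1628)^(1/3) = 1.054
- To 18%: (0.2195/0.1628)^(1/3) = 1.105
- To 22%: (0.2821/0.1628)^(1/3) = 1.201

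For chi-square, the non-centrality is λ = N·Σ(p − e)²/e, where p are the cell probabilities and e their values under independence. For the trend test it is λ = N·ρ², where ρ is the correlation of the row and column scores (midranks for PA). Power is the upper tail of the non-central chi-square beyond its 5% critical value.

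| Outcome | N | Top level, 14% to | λ chi-square | Power, chi-square | λ trend | Power, trend |
|---|---|---|---|---|---|---|
| Five levels | 3,000 | 18% | 8.08 | 41% | 8.06 | 81% |
| Five levels | 15,000 | 16% | 11.15 | 56% | 11.15 | 92% |
| Five levels | 15,000 | 22% | 136 | about 100% | 135 | about 100% |
| Binary | 3,000 | 18% | 3.57 | 32% | 3.57 | 47% |
| Binary | 15,000 | 16% | 4.66 | 41% | 4.66 | 58% |
| Binary | 1,250 | 22% | 5.54 | 48% | 5.52 | 65% |

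**Sensitivity.** With other assumed distributions (PA 8/14/36/28/14%, years 55/25/12/8%), an odds ratio of 1.10 per year at N=3,000 gives 38.6% against 77.9%. Simulation of the same case gives 37.3% against 78.9%. At N=15,000 it is 99.6% against over 99.9%. An odds ratio of 1.05 at N=15,000 gives 51.0% against 88.0%.

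**When the trend assumption fails.** Keep the first set of inputs at N=3,000 and use equally spaced scores. Let the odds ratios against the first year be 1, 1.35, 1 and 1/1.35, where 1.35 = 0.2195/0.1628. This rise and fall gives chi-square about 93% power and the trend test about 14%.

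**The case against.** A reader might infer that the whole dose question goes without direction or effect size. The article does not support that. The cross-table is offered as an example, the same exposures are also applied to continuous PA, and longitudinal and adjusted analyses are planned. These can supply both direction and size. That they name no model is normal for a condensed article and is not part of this point. This limit on scope stands.

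The size of the loss is also open to challenge:
- The 5×4 table is an assumption. The section's one explicit categorical PA outcome is binary, and there the gap is about 15 to 17 points in the settings shown. With two year groups and binary PA, chi-square already has one degree of freedom and nothing is lost.
- The N of 1,250 to 3,000 reflects sampling that ended when all consenting girls began to be invited in 2019–2020. However, 15,000 is only the number who can be invited by email, and the article itself concedes possible participation bias. Analysed samples well below 15,000 are plausible.
- The calculation assumes a steady trend, which favours a trend test. The Background says girls disengage more steeply as they move through adolescence, and girls with more years will tend to be older. The crude relation could be flat, reversed or non-monotone, and in the last case chi-square can win clearly.
- An unadjusted odds ratio per year would mix participation with ageing and self-selection.

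The last two arguments shape the remedy but do not rescue the named test. Percentages in the cross-table would show a direction, but the test would still not assess it.

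**Conclusion.** The point holds for the one named comparison. Chi-square or Fisher's exact is the only test the article gives for PA category by years of participation; it discards the order of both and gives no direction or effect per year at any sample size.

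The power loss is conditional. For a monotone relation it is about 36 to 40 points with five PA levels in the headline settings and about 15 to 17 with the binary outcome. It vanishes at 15,000 responders for a rise to 22%. These figures rest on assumed PA and year distributions, a proportional-odds trend, alpha 0.05 and no school clustering. It would be wrong to conclude from them that the study as a whole is underpowered or cannot address dose. The importance is minor to moderate.

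**What to change.** For PA category by years of participation, and for PA level by activities per year, replace the chi-square or Fisher test as the inferential analysis with a model that uses the order:
- Five-level item: proportional-odds model, logit P(PA ≥ k) = α_k + β·years + γ·(age or grade).
- Binary outcome of meeting the recommendation: logistic model with the same terms.

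Enter years as an ordered score and report exp(β), the odds ratio per year, with its confidence interval. Describe it as an association and not as a program effect, since self-selection remains after adjusting for age or grade. Treat activities per year in the same way.

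Keep the cross-table as description and the chi-square as a check for departure from trend, because a one-degree-of-freedom test is weak against a non-monotone relation. Chi-square and Fisher remain suitable for truly unordered variables.

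The cost is a sentence or two in the analysis section and standard software. No new data are needed, as Table 1 already lists age and school grade.
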